#### Primary and secondary analyses

The primary outcome QOLLTI-F of the care-giving parents 1 month after study inclusion will be analysed by a linear mixed-effects model with QOLLTI-F at baseline and group (SPPC vs. comparison) as fixed effects. A random intercept will be modelled per patient (to account for the non-independence of parents from the same patient). In addition, all measurements of QOLLTI-F taken at different follow-up visits will be analysed by a linear mixed-effects model as above, but with an additional random intercept per parent (to additionally account for the non-independence of multiple measurements per parent).

To adjust the effect size estimate for SPPC vs. comparison for potential confounders, we will use propensity score weighting. Potential confounders were already identified and include characteristics of the patient (diagnosis, age, sex), disease duration, family system (sense of coherence, family hardiness), sociodemographic variables of the family (e.g. parental living situation, family income), and contextual information (e.g. study site characteristics). As a sensitivity analysis, we will add the most important confounders as covariates in the statistical models (analysis of covariance approach).

Secondary endpoints will be analysed by linear mixed-effects models or generalised linear mixed-effects models (in case of non-normal error distribution). Normal linear models or generalised linear models may be used for secondary outcomes measured only once per patient. Sensitivity analyses will be performed as applicable and appropriate.

Missing measurements of the primary outcome, QOLLTI-F at 1 month, will be multiply imputed, based on measurements taken at 2 weeks (first follow-up measurement) and available patient characteristics.

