### Participants and recruitment

#### Patients and families

Children suffering from a life-limiting condition and potentially in need of SPPC, their parents and siblings, as applicable, were eligible to enter the study under the following inclusion criteria: 1) children, aged 0–18 years; parents (mothers and/or fathers) of included children; 2) siblings, aged 8–18 years, of included families; 3) proficiency in German or French language. Neonates with medical complications due to prematurity and/or birth complications and treated in a neonatal intensive care unit and patients enrolled in the SPPC programme with an expected life expectancy of < 48 h were excluded due to limited exposure time. Additionally, children and their families under child protection regulations were not eligible.

For the intervention site, all children entering the SPPC programme, after referral by a member of the frontline care team (usually a physician), were prospectively and consecutively screened for eligibility and invited for study participation. Recruitment was then performed by a member of the SPPC team within the first 2 weeks of SPPC initiation.

For the comparison sites, recruitment started in February 2020 and was performed by specialists of various medical disciplines, e.g. neurology or oncology after evaluating the potential need for SPPC of their patients. This need was defined per indication criteria of the SPPC programme at the intervention site and read as follows: 1) increase in (unplanned) hospital admissions during the last months; 2) adverse medical events from which the child is not recovering completely; 3) increasing symptom burden; unsatisfactory response to treatments; 4) conflicting treatment goals; 5) estimated life expectancy less than 6–12 months; 6) patient’s/parents’ wish for PC support [26].

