#### Patients and families

Since a large proportion of the study population is young or cognitively impaired, we defined caregiver QOL as the primary outcome. Each participating patient/family is followed for a maximum time of 1 year as long as the child is alive. Assessment timepoints are dynamic, starting with two bi-weekly assessments, followed by four monthly assessments and three-monthly after that. For families, who lose their child during the study, bereavement follow-up continues for another year with four assessments. All outcomes on the family level are assessed as surveys with self-reported and validated questionnaires on paper. Questionnaires are distributed in the hospital or sent home by the study team in case the child is at home at the time of a study assessment. Outcomes on the patient level are assessed as proxy measures through the parents, unless the patient is capable to report her−/himself. Siblings’ QOL is only assessed, if they are able to self-report.

Service outcomes are assessed through the collection of routine data via chart review at assessment timepoints. This includes patient-specific information related to healthcare resource utilization, e.g. hospital admissions and length of stays, procedures, and diagnostic information and date of death. Economic outcomes are assessed through queries for each patient for costs on the healthcare system level (hospitals, formal payers) and through self-reported direct and indirect health-related expenditure data (questionnaire) from participating families.

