## Discussion

This study evaluates the effectiveness of SPPC and its impact on patient-, family-, health professional-, and healthcare-related outcomes. The study will contribute to current knowledge by providing relevant outcome data based on the assessment of SPPC services within a comparative effectiveness research framework. Reporting on outcome metrics at the family level and providing detailed contextual information on healthcare provision has the potential to guide the expansion and sustainability of services and improve the quality of care for children with life-limiting conditions and their families internationally.

Determining clinical effectiveness will require prospective studies using comparison groups to establish the relationship between the receipt of SPPC and selected outcomes on the client and service levels [23]. However, the classical randomised controlled trial study design with its origin in establishing the efficacy of new drugs under controlled situations falls short in evaluating the effectiveness of a complex intervention in a real-world setting. Effectiveness research broadens the design options for evaluating interventions by possibly loosening up some of the rigorous control measures mandatory in a randomised controlled trial and therefore trading off strong internal validity in favour of generalisability (external validity) [40]. The consequence of less rigorous controls is an increased risk of confounding, which may limit causal interpretation of the study results.

Dealing with potential imbalance between intervention and comparison group will likely be this study’s greatest challenge. We will take all possible and reasonable measures, e.g. propensity scoring, multilevel modelling to ensure justified group comparisons and interpretation. The study’s rich longitudinal data over a period of approximately 1 year will allow a unique reporting on courses of illness of the child, of the QOL of close family members and the family’s financial hardships.

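### The additional all-visits QOLLTI-F model has no visit term: its group coefficient can absorb a time trend if follow-up differs between groups, and it cannot show an effect that changes over the year

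*Protocol article*

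**What the plan says.** Under Primary and secondary analyses, the QOLLTI-F at 1 month "will be analysed by a linear mixed-effects model with QOLLTI-F at baseline and group (SPPC vs. comparison) as fixed effects", with a random intercept per patient. The next step is introduced as an addition: the QOLLTI-F measurements from all follow-up visits "will be analysed by a linear mixed-effects model as above, but with an additional random intercept per parent". The one stated change is that further random intercept for each parent. No visit, time or group-by-time term is named. Propensity score weighting is planned for patient, disease, family and site characteristics, none of which says when a measurement was taken.

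Table 2 places the QOLLTI-F follow-up visits at days 15, 30, 60, 90, 120, 150, 240 and 330. The text under Outcomes and procedures describes the same schedule as "starting with two bi-weekly assessments, followed by four monthly assessments and three-monthly after that". Follow-up depends on survival: "Each participating patient/family is followed for a maximum time of 1 year as long as the child is alive". One of the indication criteria under Participants and recruitment is "estimated life expectancy less than 6–12 months".

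**The concern.** By referring back to the 1-month model and naming one change, the article fixes the fixed effects of the longitudinal model; it does not leave them open. A model built for a single time point is then applied to eight time points. Two consequences follow, and they rest on different conditions.

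First, families whose child dies early contribute only early visits. The groups are formed by site and recruited differently: at actual entry to the SPPC programme on one side, on a specialist's judgement of potential need on the other. Their survival may therefore differ. If caregiver quality of life also moves over time, the group with shorter follow-up is measured on average at an earlier stage, and that difference enters the group coefficient.

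Second, even with identical survival, one coefficient is one average over days 15 to 330, weighted towards the early visits (six of the eight fall by day 150). It cannot show whether a benefit builds up, wears off or reverses. This is the only stated analysis that uses all QOLLTI-F follow-up.

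**Working it through.** **The plan's own figure.** Variance per patient is 1.7² × (1 + 0.8)/2 = 2.601 with two parents and 1.7² = 2.89 with one. The 70/30 mix gives 1/(0.7/2.601 + 0.3/2.89) = 2.681, an SD of 1.64. For a 1-point difference at two-sided 0.05 (sidedness assumed), power is 0.799 with 86 patients and 0.809 with 88; 88/0.9 = 97.8, so 98. The stated sample size reproduces. It concerns the 1-month comparison only and does not depend on this point.

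**Inputs for the longitudinal model.** From the document: the Table 2 visit days, 70% of patients with two parents, and SD 1.7. Assumed, because the document gives none of them: exponential survival, a linear trend common to both groups, death unrelated to QOLLTI-F within group, no true effect, and a variance split of 1.6 (patient), 0.3 (parent) and 0.99 (residual), which sums to 2.89. Baseline QOLLTI-F is left out of this calculation.

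**Step 1: mean visit day by number of visits completed.** For the first k = 1 to 8 visits: m_k = 15, 22.5, 35, 48.75, 63, 77.5, 100.7, 129.4.

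**Step 2: weighting.** The probability of exactly k visits is p_k = S(t_k) − S(t_{k+1}), with p_8 = S(330). A family with k visits and q parents gets weight w = 1/[1.6 + (0.3 + 0.99/k)/q]. The weighted mean visit day in a group is M = Σ p_k w m_k / Σ p_k w, taken over the 70/30 mix of q = 2 and q = 1.

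**Step 3: bias.** Bias = slope per day × (M in SPPC − M in comparison). The slope is −1/330 or −2/330.

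| Survival, comparison vs SPPC | M, comparison vs SPPC (days) | Bias, 1-point fall | Bias, 2-point fall |
|---|---|---|---|
| equal | equal | 0 | 0 |
| median 365 vs 300 days | 100.9 vs 96.1 | 0.015 | 0.03 |
| median 365 vs 240 days | 100.9 vs 90.0 | 0.03 | 0.07 |
| median 365 vs 180 days | 100.9 vs 81.2 | 0.06 | 0.12 |
| alive at day 330: 80% vs 60% | 117.9 vs 105.3 | 0.04 | 0.08 |
| alive at day 330: 80% vs 40% | 117.9 vs 91.1 | 0.08 | 0.16 |
| alive at day 330: 90% vs 40% | 123.7 vs 91.1 | 0.10 | 0.20 |
| median 365 vs 120 days (severe) | 100.9 vs 67.8 | 0.10 | 0.20 |
| median 1000 vs 100 days (extreme) | 117.6 vs 61.8 | 0.17 | 0.34 |

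A trend of 0.1 to 0.2 points per 30-day month is a fall of 1.1 to 2.2 points over 330 days, so it makes each entry 10% larger; 365 vs 120 days then gives 0.11 to 0.22. A rising trend, or shorter survival in the comparison group, reverses the sign. The variance split matters little: placing 0.8 × 2.89 = 2.31 at patient level, in line with the protocol's correlation between parents, leaves 365 vs 120 days at 0.10 and 0.20. With categorical visit in the model, the bias is 0.00 in every scenario recomputed that way.

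**Step 4: a changing effect with equal survival (60% alive at day 330 in both groups).** M/330 = 105.3/330 = 0.32.
- Effect growing linearly from 0 to 1 point: reported as 0.32.
- Effect fading from 1 to 0: reported as 1 − 0.32 = 0.68.
- Effect reversing from +1 to −1: reported as 1 − 2 × 0.32 = 0.36, an apparent benefit.

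A visit main effect alone leaves these values unchanged. Only a group-by-visit term shows the pattern.

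**The case against.** The strongest reply is that this is a supplementary analysis. The hypothesis, the sample size and the primary test concern one time point, 1 month, where no visit term is needed. A reader might infer that the trial's main result is biased; the document does not support that, and the reply stands in full.

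The second reply is that bias is not shown. It needs unequal follow-up and a trend in caregiver quality of life together, and the article reports neither. The comparison sites apply the indication criteria of the intervention site, which aims at similar patients. A threefold gap in median survival is a severe assumption, and smaller gaps give small biases. This also stands: the bias is a conditional risk of modest size. It does not touch the second consequence, which needs neither condition.

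A reader might also infer that the Discussion contradicts the model, since it says the "rich longitudinal data over a period of approximately 1 year will allow a unique reporting on courses of illness of the child" and names the quality of life of close family members as well. That remark concerns what the data permit. It is not tied to this model, and a visit-by-visit description would satisfy it. It is not a contradiction.

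Finally, a journal article condenses, and the full plan may contain a visit term. That would be a sufficient answer had the article been silent. Here it states the fixed effects by reference, so if the full plan differs, the published sentence needs correcting.

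**Conclusion.** The point holds for the additional all-visits QOLLTI-F analysis and for nothing else. As stated, that model has no visit term. Whether this biases the group coefficient depends on two facts the document does not give: survival by group and the course of caregiver quality of life. Under a fall of 1 to 2 points over 330 days, the bias is about 0.02 to 0.20 points for moderate survival differences. In the two severe scenarios it is 0.10 to 0.17 at the milder trend and 0.20 to 0.34 at the steeper one, against a 1-point target difference. It is zero if either condition fails, and its sign depends on the direction of both. The claim that unequal survival by itself biases the estimate is too strong.

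That one coefficient hides a growing, fading or reversing effect holds without these assumptions; only the figures 0.32, 0.68 and 0.36 depend on the survival and variance values chosen. This merits a change before analysis but does not threaten the primary result.

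**What to change.** In the all-visits model, add visit as a categorical fixed effect, which removes the timing bias, and a group-by-visit interaction, which shows a changing effect. Report the group difference at each scheduled visit, together with one average over visits named in advance with its weights. Interpret these as effects while the child is alive.

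The cost is 7 parameters for visit and up to 7 for the interaction, and no new data. Days 240 and 330 may be sparse and may need grouping by a rule set beforehand; an average with equal visit weights would give those thin visits full weight, so the choice should be deliberate. The change does not cure bias from deaths or withdrawals that are themselves related to quality of life.

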## Methods

### Design and setting

This study applies a quasi-experimental design within the framework of comparative effectiveness research, exploring the effectiveness of SPPC as a complex intervention in comparison with routine care provided in a non-specialised PPC environment. The study takes place at four study sites: the largest Swiss University Children’s Hospital with a longstanding established dedicated SPPC programme serves as the intervention site, two other Swiss university children’s hospitals and a Cantonal children’s hospital providing general PPC and are just developing SPPC comprise the comparison sites. Recruitment took place between November 2019 and May 2022, and the longitudinal data collection is ongoing until May 2023. An overview of the study’s setup, timeline and outcomes is provided in Fig. 1.

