### Intervention and comparison

The service of a SPPC team is considered as a complex intervention with components on various levels and of variable dosing, based on the needs of each individual patient and her/his family. All services provided to patients/families by a member of the multiprofessional SPPC team at the University Children’s Hospital in Zurich are considered as study intervention. This includes direct medical, nursing, social, and psychological and spiritual consultations of the patient/family, as well as patient−/family-related consultation of the frontline care team. Bereavement support, as integrated part of SPPC is routinely offered at the individual or group level as appropriate for parents and siblings. The programme at the intervention site offers full 24/7 services from the SPPC team’s physicians, nurses and psychologists and includes home visits.

For patients/families in the comparison group (Aarau, Basel, Berne) routine care is provided as per established paediatric standards in a generalised PPC environment (provided by disease specific specialists with some PPC training [3]) already in place at all study sites. In all of the three comparison sites a PPC team is available since 2019/2020. However, these developing teams differ on the level of capacity, i.e. few human resources and mostly professionals with basic training and experience in PPC without being fully engaged in PPC, no 24/7 coverage, and limited psychologist and bereavement support.

Assignment to study groups will happen naturally, determined through the recruiting study sites. As this study is conducted in a natural environment with continuous development of care practices, adaptations of care structures and processes at all study sites are possible and probable during the duration of the study. No restraints of this natural evolution will be superimposed by the study. Care context is assessed on yearly basis in all four participating study sites, described and used as instrumental variables estimation as applicable.

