### Data management, monitoring and risks

The sponsor-investigator is implementing and maintaining quality assurance and quality control systems to ensure that the study is conducted and data are generated, documented (record), and reported in compliance with the protocol, good clinical practice, and applicable regulatory requirement(s). Data extracted from the patient charts will be entered into an internet-based secure data base secuTrial® developed in agreement to the Good Clinical Practice guidelines provided by the Clinical Trials Centre Zurich. Person data will be pseudonomised through secuTrial®. Local coordinators will be assigned to assist with and facilitate logistics concerning the availability of medical charts and workspace in each participating study site. Data collectors will receive instructions and training before the start of data collection to assure and enhance data quality. Furthermore about 5% of the charts will be randomly chosen and data will be collected by two different people for quality checking.

A quality assurance audit/inspection of this study may be conducted by the competent ethics committee. The quality assurance auditor/inspector will have access to all medical records, the investigator’s study related files and correspondence, and the informed consent documentation that is relevant to this clinical study. We consider the risk for participants in this study as minimal. Allocation to intervention and comparison groups is determined by the natural environment of the four study sites’ care services.

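### Group is fixed by site, so site characteristics unique to the intervention site cannot enter the propensity score, and care context cannot serve as an instrument for the group contrast

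*Protocol article*

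**What the plan says.** Design and setting gives the structure: "The study takes place at four study sites". One hospital, "with a longstanding established dedicated SPPC programme serves as the intervention site", and three hospitals "providing general PPC and are just developing SPPC comprise the comparison sites".

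Intervention and comparison states the allocation rule: "Assignment to study groups will happen naturally, determined through the recruiting study sites". Data management, monitoring and risks repeats it: "Allocation to intervention and comparison groups is determined by the natural environment of the four study sites".

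Primary and secondary analyses names the method: "To adjust the effect size estimate for SPPC vs. comparison for potential confounders, we will use propensity score weighting". It says that the potential confounders have already been identified. Besides patient, disease, family and sociodemographic variables, the list includes "contextual information (e.g. study site characteristics"). The most important confounders are also to be added as covariates in a sensitivity analysis.

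For care context, assessed yearly at all four sites, Intervention and comparison adds that it will be "described and used as instrumental variables estimation as applicable".

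**The concern.** Propensity score weighting requires that patients with a given covariate pattern could have been in either group. Here the probability of SPPC is 1 at one site and 0 at the other three. A covariate that identifies the intervention site therefore removes overlap by design, whatever the sample size.

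The contextual features that the article describes are of this kind. Intervention and comparison contrasts round-the-clock cover, team capacity, and psychologist and bereavement support at the intervention site with their absence or limitation elsewhere. Design and setting adds that the intervention hospital is the largest.

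The instrumental-variable clause meets the same obstacle. An instrument must move treatment, share no causes with the outcome, and act on the outcome only through treatment. Care context follows site, is partly the intervention itself, and can affect caregiver quality of life directly; quality of care and environment are domains of the primary instrument (Table 1).

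The groups are not randomised and are recruited differently: by the SPPC team at one site and by disease specialists at the others. The Discussion calls imbalance probably the greatest challenge and names propensity scoring first among the remedies. If the score fails, the main planned protection against confounding is lost, or is rebuilt after the data have been seen.

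**Working it through.** **Inputs from the article.** One intervention and three comparison sites; group determined by site; 49 patients planned per group. The article gives no figure for the propensity model, so the group size is the only planned figure used. It reproduces from the article's assumptions: effective SD = 1.7 × √[1/(0.7/0.9 + 0.3)] = 1.638; 44 per arm by the t distribution (power 0.808), 88 in total; 88/0.9 = 97.8, rounded up to 98.

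**Assumptions, not in the article.** Comparison patients split 16/17/16 by site; simulated patient covariate, outcome and site sizes.

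**1. Propensity scores.** Logistic model for group:

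| Covariates | SPPC scores | Comparison scores |
|---|---|---|
| Patient covariate only | 0.23–0.75 | 0.15–0.75 |
| Plus 24/7 cover | 1 | 0 |
| Plus site size, intervention site largest | 1 | 0 |
| Plus site indicators | 1 | 0 |
| Plus university vs cantonal status | 0.17–0.92 | 0 at the cantonal site, up to 0.87 overall |

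The middle three rows separate completely. In the last row overlap survives between the intervention site and the two university comparison sites, but the cantonal patients have no counterpart.

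**2. Weights when the score e is 1 or 0.**
- Inverse probability: SPPC 1/e = 1/1 = 1; comparison 1/(1 − e) = 1/1 = 1. The weighted and unweighted analyses are identical.
- ATT: SPPC 1; comparison e/(1 − e) = 0/1 = 0. The comparison group has no weight.
- Overlap: SPPC 1 − e = 0; comparison e = 0. Nobody has weight.

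The article does not say which weights are meant. The first fails silently, the other two visibly.

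**3. Covariate-adjusted sensitivity analysis.** A yes/no characteristic present only at the intervention site is the same column as group, so the two coefficients cannot both be estimated. Site indicators give the same result. A graded characteristic such as size leaves a group coefficient only by extrapolating a trend across three comparison sites.

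**4. Instrument.** The Wald estimator is the outcome difference across levels of the instrument divided by the treatment difference. With site as instrument the denominator is 1 − 0 = 1, so the estimate is the crude difference: 0.614/1 = 0.614 in the example. Year-to-year change within a site moves no patient between groups, so it is not relevant to the contrast either.

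**5. What remains unadjustable.** Suppose there is no true effect, the model has no site term, and a share ρ of outcome variance lies between sites (ρ is assumed). On the standardised scale the site part of the variance of the group difference is ρ(1 + 1/3), and the patient part is (1 − ρ)(2/49). At ρ = 0.05 these are 0.067 and 0.039, although the model counts essentially only the second. Simulated type I error was about 0.05 at ρ = 0, 0.09 at 0.01, 0.22 at 0.05 and 0.35 at 0.10.

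**The case against.** Several stronger readings are tempting, and the documents do not support them.

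- **A reader might infer that any site characteristic forces scores of 0 or 1.** The article names no specific site variable, and it gives 24/7 cover and capacity as descriptions of the care compared, not as score covariates. University status does not by itself separate the groups. The problem attaches to characteristics, alone or combined, that are unique to the intervention site.
- **A reader might take the 49 versus 49 example as a forecast.** It is not. An indicator equal to group separates by construction, and weights of 1 arise only with inverse-probability weighting.
- **A reader might conclude that nothing would be adjusted.** The primary model includes baseline QOLLTI-F, and patient and family terms in the covariate-adjusted analysis remain estimable. What is lost is the contribution of the weights.
- **A reader might infer that an instrumental-variable result will be presented as causal.** The clause is conditional, no such analysis appears under Primary and secondary analyses, and it is not stated that the yearly care context and the listed contextual confounders are the same variables. The Discussion concedes that confounding may limit causal interpretation.

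It is also fair that the final covariate list, overlap checks and trimming commonly belong in an analysis plan, which is not shown. Their absence is not criticised here. What stands is the stated text: site characteristics are listed as already identified confounders for the weighting, and care context is offered as an instrument, although site fixes group. The Discussion does not acknowledge that the two cannot be separated. The multilevel modelling that it mentions cannot separate them either, with one treated site.

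**Conclusion.** The point holds in this limited form. If any characteristic or combination unique to the intervention site enters the score, overlap is lost completely: the weights add no adjustment or yield no estimate. Shared characteristics do less harm but can still remove overlap for some comparison sites. Care context is not a valid instrument for the group contrast, and a site-level instrument reproduces the crude difference.

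These conclusions follow from the allocation rule and need no assumed figure. The score ranges, the 0.614 and the type I error rates are illustrations that rest on the assumptions listed in the check; the error rates in particular depend on a between-site variance that the article does not give. The defect lies in what the article states, not in detail that it leaves out.

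**What to change.** - Build the propensity score from baseline patient and family variables only.
- Keep site characteristics out of the score and out of the covariates in the sensitivity analysis. This also excludes shared characteristics, which need not separate the groups but can still remove overlap for some sites.
- Delete the instrumental-variable clause and report yearly care context descriptively.
- State that the estimated SPPC effect cannot be separated from other differences between the single intervention site and the comparison sites.

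This changes analysis wording only and needs no new data or patients. The price is an explicit concession that site-level confounding is not adjustable. Setting the intervention site against each comparison site in turn is optional and descriptive only: with an even split, 49/3 gives about 16 comparison patients per site, against 49 planned for the powered comparison.
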